## 2.1 Primary Objective

This is a Pilot Study to designed to support future expanded Pivotal Studies of the device.

**Primary Aim 1 examines the efficacy of sequential bilateral aTBS compared to sham stimulation for suicidal ideation in adolescents with MDD. The Columbia Suicide Severity Rating Scale (C-SSRS) severity of ideation subscale is the primary acute outcome measure. Additional outcome measures include monthly follow-up C-SSRS severity of ideation subscale scores, number of hospitalizations, and number of emergency department visits related to suicidal ideation over a 12 month follow-up period.**

- **Hypothesis 1a:** We expect 10 days of sequential bilateral aTBS will have greater efficacy for improving suicidal ideation in adolescents with MDD (as assessed by the C-SSRS severity of ideation subscale) over the 10-day acute treatment trial compared to sham stimulation.
- **Hypothesis 1b:** We expect that adolescents who receive 10 days of sequential bilateral aTBS will have lower suicidal ideation (as assessed by the C-SSRS severity of ideation subscale) over the 12-month follow-up period compared to sham stimulation.
- **Hypothesis 1c:** We expect that adolescents who receive 10 days of sequential bilateral aTBS will have fewer emergency department visits and fewer hospitalizations related to suicidality during the 12-months after the intervention compared to sham stimulation.

## 2.2 Secondary Objective

**Secondary Aim 2 examines TMS-EMG LICI as a predictive and target engagement biomarker for suicidality in adolescents with MDD.**

- **Hypothesis 2a:** We expect that cortical inhibition (as assessed by pre-treatment LICI-100 collected with TMS-EMG) will have an indirect relationship with severity of

suicidal ideation (as assessed by the C-SSRS severity of ideation subscale) in all subjects at baseline.

- **Hypothesis 2b:** We expect that, among the adolescents who receive active sequential bilateral aTBS treatment, there will be an indirect relationship between cortical inhibition (as assessed by LICI-100, TMS-EMG) and suicidal ideation (as assessed by the C-SSRS severity of ideation subscale) over the 10 day acute treatment trial.

**An exploratory Aim focuses on developing TMS-EEG measures of cortical inhibition (TMS-EEG N45 and N100) for assessing suicide risk and responsiveness to aTBS in adolescents with MDD.**

This is the first study to examine sequential, bilateral accelerated TBS in depressed adolescents with suicidal ideation. Sequential bilateral aTBS and the proposed panel of biomarkers will be rapidly implemented in the clinic. This novel approach will facilitate a critical paradigm shift toward brain-based approaches for assessing and treating suicidal ideation in adolescents with MDD.

### 3 Study Design

#### 3.1 General Design

This pilot study is a randomized, double-blind, sham-controlled trial of sequential bilateral aTBS in adolescents with depression and suicidal ideation (Figure 7). Three sessions are administered daily for 10 days (5 days per week). During each session, cTBS in which 1800 pulses are delivered continuously over 120 seconds to the right dorsolateral prefrontal cortex (RDPFC) is administered first, followed by iTBS in which 1800 pulses are delivered in 2 second bursts, repeated every 10 seconds for 570 seconds (1800 pulses) to the left dorsolateral prefrontal cortex (LDPFC). The TBS parameters were adopted from prior work, with 3-pulse 50 Hz bursts given every 200 ms (at 5 Hz) with an intensity of 80% of active MT. The comparison group will receive 3 daily session of bilateral sham TBS treatment for 10 days.

[figure not shown]

**Figure 7. Study Overview**

**aTBS, Accelerated Theta Burst Stimulation**

**CDRS-R, Children's Depression Rating Scale Revised**

**C-SSRS, Columbia-Suicide Severity Rating Scale**

**MINI, The Mini-International Neuropsychiatric Interview (for age 18) or the Mini-International Neuropsychiatric Interview for Children and Adolescents (for ages 12-17)**

**TBS, Theta Burst Stimulation**

**TMS-EEG, Transcranial Magnetic Stimulation with Electroencephalography**

**TMS-EMG, Transcranial Magnetic Stimulation with Electromyography**

All subjects will receive standard of care treatment for depression and suicidal ideation including daily psychotherapeutic skill sessions (Figure 8). The 10-day psychotherapy treatment program was adapted from recent work and input from a consultant ([name]). The primary outcome measure is suicidal ideation assessed with the C-SSRS severity of ideation subscale. Depressive symptom severity will be assessed with the CDRS-R.

| Session | Participants          | Topic                                              |
|---------|-----------------------|----------------------------------------------------|
| 1       | Adolescent and Parent | Chain analysis and safety plan                     |
| 2       | Adolescent and Parent | Review adherence, psychoeducation, and safety plan |
| 3       | Adolescent            | Reasons for living module                          |
| 4       | Adolescent            | Mindfulness module                                 |
| 5       | Adolescent            | Distress tolerance module                          |
| 6       | Adolescent and Parent | Review sessions 3-5 with parent                    |
| 7       | Adolescent            | Problem-solving module                             |
| 8       | Adolescent            | Socialization and support module                   |
| 9       | Adolescent            | Wellness and relapse prevention module             |
| 10      | Adolescent and Parent | Review work with parent                            |

**Figure 8. Psychotherapy Sessions**

### 3.2 Primary Study Endpoints

The primary aim examines the efficacy of sequential bilateral aTBS compared to sham stimulation for suicidal ideation in adolescents with MDD. The Columbia Suicide Severity Rating Scale (C-SSRS) severity of ideation subscale is the primary acute outcome measure. Additional outcome measures include monthly follow-up C-SSRS severity of ideation subscale scores, number of hospitalizations, and number of emergency department visits related to suicidal ideation over a 12 month follow-up period.

### 3.3 Secondary Study Endpoints

The secondary aim examines TMS-EMG LICI as a predictive and target engagement biomarker for suicidality in adolescents with MDD. An exploratory aim will examine TMS-EEG N45 and N100 measures for assessing suicide risk and responsiveness to sequential bilateral aTBS in adolescents with MDD.

### 3.4 Primary Safety Endpoints

Data will be collected to determine:

- Incidence of emergency department and hospitalizations related to suicidality over a 12-month period.
- Incidence of adverse events, serious adverse events, and unanticipated adverse device effects.
- Any changes in cognition associated with treatment as assessed by the NIH Toolbox Cognition Battery.
- Any changes in auditory threshold assessments associated with treatment.

## 4 Subject Selection, Enrollment and Withdrawal

Adolescents with MDD and suicidal ideation will be recruited from the general community and referrals from local providers. Currently [name] directs a research program and outpatient clinic for adolescent mood disorders. It is anticipated that adolescents with MDD and suicidal ideation will also be recruited from an eighteen bed child and adolescent psychiatry unit within Mayo Clinic. Our research group historically has been successful in the recruitment of similar samples. Based on prior experience it is anticipated that 200 patients will be screened and 100 will be enrolled to reach the target sample size of 80 needed to complete this pilot study.

### 4.1 Inclusion Criteria

Patients are eligible for participation if they are:

- Inpatients or outpatients
- Voluntary clinical patient with the capacity to assent (or consent if 18) to treatment and a parent or legal guardian with the capacity to consent (if younger than 18)
- Biological female or male (nonbinary or other gender identities are not exclusionary)
- 12-18 years of age
- Diagnosed with MDD based on Diagnostic and Statistical Manual for Mental Disorders, 5th edition (DSM-5) criteria with the Mini-International Neuropsychiatric Interview for Children and Adolescents (MINI Kid) in subjects 12-17 years of age; The Mini-International Neuropsychiatric Interview will be used for subjects who are 18 years of age
- In a current episode of MDD with duration of at least 4 weeks but less than 3 years
- Depressive symptom severity as demonstrated by CDRS-R total composite score of Forty or greater and a suicidal ideation score of 3 or more on item 13 of the CDRS-R
- A minimum score of 1 (“wish to be dead”) on the C-SSRS severity of ideation subscale
- Demonstrating that depressive symptom severity as evaluated at the screening visit does not improve between screening and baseline by 25% or more
- Eligible for transcranial magnetic stimulation (TMS) based on safety criteria
- On a medically acceptable form of birth control during the 10 day acute treatment course if female and of child bearing potential
- Taking an antidepressant medication if recommended by the referring clinician and agreed upon by parents and patients. Please note that patients are not required to take an antidepressant medication for study participation for practical, ethical, and human subject protection concerns. Medication status and prior treatment resistance will be carefully recorded with the Antidepressant Treatment History Form criteria for relevant statistical considerations.

### 4.2 Exclusion Criteria

Patients are not eligible for participation if they have:

- Diagnosis of bipolar disorder, anorexia nervosa, bulimia

nervosa, substance use disorders within the past year (with the exception of caffeine and tobacco)

- Lifetime diagnosis of a psychotic disorder confirmed by a research screening interview (including schizophrenia, major depressive disorder with psychotic features, and bipolar disorder with psychotic features)
- Intelligent quotient less than 70 (if there is a clinical concern, subjects will be psychometrically assessed with the Slosson Intelligence Test, Revised)
- Positive urine drug screen at baseline
- Patients with a history of epilepsy or unexplained seizures
- Any family history of epilepsy
- Patients medicated with drugs lowering the seizure threshold (examples: neuroleptic agents and tricyclic antidepressants)
- History of any treatment with electroconvulsive therapy or TMS
- Use of any investigational drug within 4 weeks of baseline
- Prior brain surgery
- Risk for increased intracranial pressure such as a brain tumor
- Life-time history of head trauma with loss of consciousness for greater than 5 minutes duration.
- Any true positive findings on the TMS safety screening form (TASS)
- Pregnant or nursing patients
- Conductive, ferromagnetic, or other magnetic-sensitive metals implanted in the head within 30 cm of the treatment coil excluding the mouth that cannot be safely removed (examples include cochlear implants, vagus nerve stimulators, deep brain stimulators, implanted electrodes/stimulators, aneurysm clips or coils, stents, bullet fragments, jewelry and hair barrettes)
- Patients with any implanted stimulators or implants controlled by physiologic signals, including VNS, SCS, PNS, defibrillators and pacemakers.
- Patients with neurological conditions that include a history of seizures, cerebrovascular disease, cerebral aneurysm, dementia, movement disorders, having a history of repetitive or severe head trauma, or with primary or secondary tumors in the CNS
- Patients with a history of increased intracranial pressure, history of severe headaches within the previous 1 year, or severe head trauma
- Implanted medication pumps and cardiac pacemakers
- Patients suffering from vascular, traumatic, tumoral, infectious, or metabolic lesions of the brain, even without a history of seizure, or without anticonvulsant medication
- 
- Patients with an unstable medical illness (other than depression)
- Inability to adhere to the protocol

### 4.3 Subject Recruitment, Enrollment and Screening

Adolescent subjects will be recruited through the Mayo Clinic Depression Center and Division of Child and Adolescent Psychiatry. This includes recruitment through outpatient clinics, an

18-bed child and adolescent inpatient psychiatry unit, and the Mayo Clinic Emergency Medicine Department. The Mayo Clinic Health Systems Clinics throughout Minnesota and Wisconsin provide additional recruitment environments. Ongoing and future outreach efforts also involve local treatment facilities in Rochester, St. Paul, and Minneapolis in Minnesota. The principal investigator ([name]) has prior and planned collaborations with the Rochester Public School System. This includes consultation with the school board. With appropriate approvals, recruitment flyers can be disseminated to the parents of all youth attending Rochester Public Schools.

During inpatient hospitalizations, outpatient visits, and emergency medicine department evaluations, a treatment team member will inform the research team and clinical attending physician of a patient's potential interest. The attending physician will review and determine whether or not a discussion of research participation is clinically appropriate. [name] or a research team member will be contacted to speak to the patient and family regarding the study and research participation. If the patient and family are interested, the research team will initiate the informed consent process.

The study team will take proactive steps to foster diversity and inclusion in recruitment efforts with respect to race, ethnicity, and gender. Local (Olmsted County) demographics suggest that of graduating students, 79.2% are White, 5.8% are Asian, 4.73% are African American, and 3.34% are Hispanic or Latino. However, it is anticipated that national patients will travel to Rochester, Minnesota for study participation. The study team will strive to recruit a sample more reflective of affected demographics. The research team will present the study to internal clinical services and external facilities during staff meetings. External efforts will be tailored to foster both community education regarding depression and suicidality in adolescents while establishing referral patterns. Mayo Clinic Institutional Review Board (IRB) approved flyers will be posted within facilities advertising the study. The research team will participate in local and national events such as Suicide Awareness Day, National Depression Day, and National Mental Health Day to facilitate community engagement and subject recruitment. [name] will continue to access and collaborate with relevant offices in the Mayo Clinic Center for Clinical and Translational Science (CCATS) such as the Office of Community Engagement (OCER). The OCER is led by [name]. [name] has ongoing contact with [name], [name], and [name] focused on present and future study recruitment. These collaborations provide local speaking opportunities. The study team engages clinical services on a weekly basis as well. When the study opens for enrollment, [name] will attend staff meetings and give presentations at local facilities. The following are three examples:

- a. PrairieCare Medical Group
- b. Fernbrook Family Center
- c. Highland Meadows Counseling Center, Inc.

[name] and the research team have extensive experience with brain stimulation research and studies of adolescents with depression. This prior experience includes the recruitment and retention of adolescents in transcranial magnetic stimulation protocols with 30-60 visits over 6-12 weeks. Our prior experience suggests that the sequential bilateral accelerated theta burst protocol in the present study will facilitate subject retention, as it is a more pragmatic schedule with 10 treatment days total. The Mayo Clinic Neuromodulation research team has the capability of offering treatment sessions over the weekend if necessary to accommodate an

adolescent's or family's schedule. The current protocol also delivers theta burst with an intensity of 80% motor threshold (as compared to standard protocols delivered at a 120% motor threshold). Treatment intensities of 80% motor threshold are more tolerable than 120%. It is anticipated that the current protocol will be more tolerable and preferred by adolescent subjects. The flexibility of scheduling and study theta burst dosing parameters will be highly effective in retaining adolescent subjects for the proposed study.

The primary investigator ([name]) will review documentation of inclusion and exclusion criteria. If not documented in the medical record during the month prior to enrollment, subjects will undergo a urine drug screen and urine pregnancy test (female subjects) during the screening or baseline visit.

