Table 3 describes the schedule of events. Table 4 describes all study assessments. The first visit is a screening visit. Informed consent and assent will be completed. A medical history, physical exam, vital signs, urine pregnancy test (if applicable) and urine drug screen will be completed. The subject's parent or guardian will not be told the results of the pregnancy test without the subject's permission. But if the study physician believes that being pregnant may cause serious health problems, they may need to tell the parent or guardian the test results. Patients with a positive urine drug screen that are not due to prescribed drugs are not eligible for study participation. The study physician will ask if the results can be shared with the parent or guardian. This information will be kept confidential if the subject chooses not to share the drug test results with the parent or guardian. The results of the urine drug test will not become part of the medical record, but the results will remain in the study record. Additional screening assessments include: the Transcranial Magnetic Stimulation Safety Screen (TASS), Antidepressant Treatment History Form (ATHF), pubertal development scale (PDS), Mini-International Neuropsychiatric Interview (MINI Kid for ages 12-17 and MINI for age 18), Young Mania Rating Scale (YMRS), Children's Depression Rating Scale Revised (CDRS-R), Columbia Suicide Severity Rating Scale (C-SSRS), Beck Depression Interview-II (BDI-2), Clinical Global Impressions Severity Scale (CGI-S), concurrent medications, adverse events, serious adverse events, demographics questionnaire, case report forms, and concurrent psychotherapy. The screening visit can occur on the same day or across 2 consecutive days based on participant preference.

## 6.2 Visit 2

After eligibility is confirmed, additional assessments will be completed (Table 3 and 4). These assessments include auditory thresholds, NIH Toolbox Cognition Battery, YMRS, CDRS-R, C-SSRS, BDI-2, Pre/Post Treatment Expectations CGI, concurrent medications, adverse events, serious adverse events, case report forms, concurrent psychotherapy. TMS neurophysiology measures are collected. The participant is randomized to the active aTBS group or sham aTBS. Coil localization (Beam F3) and motor threshold procedures are completed. The participant will complete day one of aTBS treatment (either 3 active sequential bilateral TBS or 3 bilateral sham treatments).

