**Clinical and Standardized Assessments:** At screening subjects will undergo a urine drug screen, urine pregnancy test, MINI-Kid or MINI interview, Brief Affective Neuroscience Personality Scale, CDRS-R, C-SSRS, Childhood Trauma Questionnaire, Clinical Global Impressions Scale (CGI), Safety Screening for TMS, Young Mania Rating Scale, Adverse Event Rating Scales, Medical History, Physical Exam, Vital Signs, Pubertal Development Scale, and the Beck Depression Inventory-II (BDI-II). At the baseline visit subjects will repeat the CDRS-R, C-SSRS, CGI, BDI-II, and Adverse Rating Scales. Other baseline assessments include the NIH Toolbox Cognition Battery, Auditory Threshold Testing, and a Pre-treatment Expectation and Experience Questionnaire. Subjects will undergo TMS-EMG testing and TMS-EEG testing at the baseline line visit. The C-SSRS (suicidal ideation severity subscale, which is the primary outcome measure) will be assessed daily for the 10 treatment days. The CDRS-R, CGI, and BDI-II will be collected weekly during the treat period (baseline, after 5 treatments, and posttreatment). After the final day of treatment, the subjects will complete the C-SSRS, CDRS-R, CGI, BDI-II, Post-treatment Expectation and Experience Questionnaire and the NIH Toolbox Cognition Battery. Vital signs will be collected at this posttreatment visit. Subjects will undergo posttreatment TMS-EMG and TMS-EEG testing. Follow-up, post-treatment assessments will be collected each month over the 12-month follow-up period. These monthly assessments will include the C-SSRS, CDRS-R, CGI, BDI-II, number of hospitalizations related to suicidality, and number of emergency department visits

related to suicidality. Concurrent medications, concurrent psychotherapy, and adverse events will be collected at every study visit.

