Any pregnancy detected during the acute 10 day treatment course or a pregnancy that may have been present during the acute 10 day treatment course (based on estimated date of conception in consultation with the subject's clinical obstetrician) will be reported within 5 business days to the IRB, DSMB, and FDA. If a pregnancy is detected during the acute 10 day treatment course no further investigational treatments will be delivered but the patient will be followed for 12 months as per the study protocol. The pregnancy outcome will be documented.

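### Section 4.3 lets a chart result from the month before enrollment replace the study urine drug and pregnancy tests, contradicting sections 6.1 and 6.4 and Table 3

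*Protocol*

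**What the plan says.** The protocol covers the two urine tests in several places.

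- **Section 4.2 (exclusions).** The drug criterion reads "Positive urine drug screen at baseline". The pregnancy criterion reads "Pregnant or nursing patients" and names no time point.
- **Section 4.3 (recruitment and screening).** "If not documented in the medical record during the month prior to enrollment, subjects will undergo a urine drug screen and urine pregnancy test"; the pregnancy test applies to female subjects. Where a test is needed, it is done "during the screening or baseline visit".
- **Section 6.1 (Visit 1, screening).** "A medical history, physical exam, vital signs, urine pregnancy test (if applicable) and urine drug screen will be completed". There is no exception for a chart result.
- **Section 6.4 (methods and measures).** "At screening subjects will undergo a urine drug screen, urine pregnancy test", again without exception.
- **Table 3.** Both urine tests are marked under screening only. The baseline, daily and posttreatment cells are empty.
- **Section 6.2 (Visit 2).** The listed assessments include neither urine test. Randomization and the first treatment day both fall at this visit.

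The contraception criterion in section 4.1 is worded as "On a medically acceptable form of birth control during the 10 day acute treatment course". Section 8 makes reportable a pregnancy detected during treatment and also "a pregnancy that may have been present during the acute 10 day treatment course".

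**The concern.** Two coordinators could each follow the protocol and do different things. One, working from section 6.1 and Table 3, tests every applicable subject at screening. The other, working from section 4.3, tests nobody who already has a chart result from the month before enrollment. Both records would show compliance with a stated rule.

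Pregnancy and a positive drug screen are safety exclusions for adolescents receiving an investigational device. The protocol treats them as serious after entry too. It stops study treatment if pregnancy is detected during the treatment course, requires pregnancy to be reported within 5 business days, and withdraws a subject with a positive drug screen during the study. Yet it does not settle when either condition is checked before first stimulation, and one of its rules allows the check to rest on an old clinical result. At stake is whether these exclusions mean the same thing for every subject.

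**Working it through.** No sample size, power or error-rate figure is involved. The check sets the passages side by side and then follows the age of the result to the first stimulation.

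**Step 1: count the timings.**

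| Source | Drug screen | Pregnancy test |
|---|---|---|
| Section 4.2 | Baseline | No time point |
| Section 4.3 | Chart result from the month before enrollment; otherwise screening or baseline | Same, female subjects |
| Sections 6.1 and 6.4, Table 3 | Screening, no waiver | Screening, no waiver, if applicable |
| Section 6.2 (Visit 2) | Not listed | Not listed |

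The drug screen has three stated timings and the pregnancy test has two.

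**Step 2: age of the result at first stimulation.** Let S be the date of screening, E the date of enrollment and V the date of Visit 2, with S ≤ E ≤ V. The protocol does not say which visit counts as enrollment.

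- Under sections 6.1 and 6.4 and Table 3, the age is V − S.
- Under the section 4.3 waiver, the age is at most 1 month + (V − E).
- The waiver therefore adds at most [1 month + (V − E)] − (V − S) = 1 month − (E − S), which cannot exceed 1 month.

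If enrollment comes before Visit 2, V − E is positive and the result can be more than a month old at first stimulation. If enrollment were taken to be randomization at Visit 2, V − E is zero and the limit is one month.

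**Step 3: is V − S bounded?** No maximum is stated. The interval need not be trivial. Section 4.1 requires that depressive severity not improve by 25% or more between screening and baseline, and section 1.5.2 provides for medication tapers for study participation.

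**Step 4: does a later rule force a fresh test?**

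- Section 5.2 holds back randomization until all entry criteria are met and pre-study procedures are complete, but it prescribes no current urine test. A subject relying on the waiver passes on the old result.
- Section 8 stops study treatment if pregnancy is detected during the treatment course, and section 8.5 withdraws for a positive drug screen during the study. Table 3 schedules neither test after screening, so detection depends on unscheduled testing or disclosure.
- The contraception criterion is worded for the treatment course and does not address the interval between test and treatment.

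None of these closes the gap.

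**The case against.** The strongest reply is that this is a narrow wording mismatch. Baseline in section 4.2 may simply mean before treatment: Table 4 says the ATHF, the MINI interviews and the TASS are collected at baseline, while Table 3 puts all three at screening. Accepting a recent clinical result is also a recognizable choice. The investigator reviews the documentation of entry criteria, randomization waits for them, and later rules act on a detected pregnancy or a positive screen. For subjects with no chart result, section 4.3 even allows a test at baseline, closer to treatment than section 6.1 requires.

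Much of this stands. The loose use of baseline would reduce the section 4.2 conflict to wording, and the safeguards lower the risk. But the section 4.3 waiver would still contradict sections 6.1 and 6.4 and Table 3, and no safeguard requires a current test.

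A reader might infer more than the document supports:

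- **That both exclusions have three timings.** Only the drug screen does, because section 4.2 gives pregnancy no time point.
- **That recent drug use is excluded.** The criteria are a positive screen and a substance use disorder within the past year.
- **That section 4.3 causes the open-ended interval.** The missing screening-to-baseline limit applies equally under section 6.1.
- **That a stated share of the 80 subjects would go untested.** The protocol gives no proportion with a chart result, and the pregnancy test does not apply to all 80.
- **That the LICI measure would be distorted, or that emergency department and inpatient recruits would mostly skip the test.** The protocol shows neither.

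**Conclusion.** The contradiction is real and lies in the current text. Section 4.3 waives study tests that sections 6.1 and 6.4 and Table 3 require, and section 4.2 refers to a drug result at a visit where none is scheduled. Followed as written, section 4.3 permits first stimulation on a drug or pregnancy result more than a month old.

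The waiver's own contribution is at most about one month beyond a test at screening. The rest of the possible delay comes from the unstated screening-to-baseline interval, which is a separate omission. The conclusion that the result may exceed a month assumes that enrollment precedes Visit 2; if the two coincide, the limit is one month and the contradiction remains. The number of subjects affected is unknown. Nothing here touches the primary comparison or its power. It is a weakness in a safety entry rule that should be corrected because correction is cheap.

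**What to change.** Reconcile sections 4.2, 4.3, 6.1, 6.4 and Table 3 so that each test has one timing, worded the same way throughout. Two routes would do this, and the choice is the sponsor's:

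1. Remove the chart-result waiver, so that section 4.3 matches the study tests that Table 3 already schedules for every applicable subject.
2. Keep it, state in all these places that a chart result may substitute, and give its maximum age counted to first stimulation rather than to enrollment.

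In either case, the drug exclusion in section 4.2 should name a visit at which a result will exist. The sponsor should also check that the period covered by the contraception criterion in section 4.1 is consistent with the timing chosen; this review does not propose what that period should be.

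The cost is a short amendment. The first route adds no procedure to Table 3 and gives up only the tests the waiver would have saved. The second adds no test to the schedule, but some chart results now accepted would be too old and those subjects would need testing. Moving the tests to Visit 2 would change Table 3 and could reveal ineligibility on the day of randomization.
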